#### LC-MS/MS Methodology

The Orbitrap Fusion mass spectrometer (Thermo Scientific) coupled with a heated electrospray ion source will be used for data acquisition. Data acquisition methods have been followed as per published protocols [41,42] with minor modifications. Briefly, for MS1 mode, mass resolution will be kept at 120,000, and for MS2 acquisition, mass resolution will be 30,000. The mass range of data acquisition will be 60 to 900 Da. Extracted metabolites will be separated on UPLC Ultimate 3000. Data will be acquired on reverse-phase and hydrophilic interaction liquid chromatography columns in both positive and negative ionization modes. HSS T3 will serve as a reverse phase column, while XBridge BEH Amide (Waters Corporation) will be used as a hydrophilic interaction liquid chromatography column. For polar compound separation, solvent A will have 20 mM ammonium acetate in the water (pH 9), and mobile phase B will have 100% acetonitrile. The elution gradient will start from 85% B to 10% B over 14 min with a flow rate of 0.35 ml/min. For reverse phase, solvent A will be water, and B will be methanol with 0.1% formic acid added in both solvents. The elution gradient will start with 1% B to 95% B over 10 min with a flow rate of 0.3 ml/min. The sample injection volume will be 5 µl. Pooled quality control samples will run after every five samples to monitor signal variation and drift in mass error.

### Data Processing

All LC-MS–acquired data will be processed using the Progenesis QI for Metabolomics (Water Corporation) software using the default settings. The untargeted workflow of Progenesis QI facilitates retention time alignment, feature detection, deconvolution, and prediction of elemental composition. The Metascope plug-in of Progenesis QI will be used for the in-house library, incorporating accurate mass, fragmentation patterns, and retention times for database searches. The study will use an online spectral library for further confirmation of identification. The retention time match cut-off will be set at 0.5 minutes, with a spectral similarity exceeding 30% for fragmentation matches in Progenesis QI. Peaks with a coefficient of variation below 30% in pooled quality control samples will be chosen for subsequent data analysis. Furthermore, manual verification of each identified feature will be conducted to select the appropriate peaks.

### Follow-Up

There are 3 in-person primary data collection points in the study: “baseline evaluation (week 0),” “postintervention assessment at 12 weeks,” and “second follow-up assessment at 24 weeks.” Between the in-person visits, participants will receive weekly telephonic follow-up calls to promote participant retention, monitor medication adherence, and collect information on any SAEs. In the case of any SAEs, participants will be instructed to discontinue the study medication immediately and to contact the study team for appropriate medical evaluation. In such scenarios, unblinding will be done by the statistician who has access to the randomization and conveyed to the treating medical team. Following completion of the 12-week intervention period, participants will return to the hospital for a comprehensive follow-up visit, which will include assessment of primary and secondary outcome measures; and blood sample collection for postintervention metabolomic analysis, and repeat laboratory investigations, including hematological, hepatic, and renal function tests. Participants will be allowed to withdraw from the study if they wish to do so, and the reason for withdrawal will be clearly documented. They will be encouraged to return the used bottles at the end of 12 weeks or if they withdraw from the study at any time point, for pill count to confirm adherence. The second follow-up assessment will take place at 24 weeks and will include detailed cognitive evaluation. Blood sampling will not be done at this time point. Participants will continue to receive posttrial standard of care from their treating physicians.

### Outcomes

The primary outcome will be change in the composite *z* score of memory between the 2 groups at 12 weeks. The memory domain will include both verbal (Verbal Learning Test: learning over trials, delayed recall, delayed recognition) and visuospatial memory (Test des Neuf Images du 93-Spatial Recall). The secondary outcomes will include alterations in metabolites, pathways, and molecular networks, and frequency of SAEs after 12 weeks of treatment with *B. monnieri*; change in *z* scores for other cognitive domains (attention, executive functioning, and information processing) at 12 and 24 weeks (including *z* score for the memory domain at 24 wk); proportion of participants in both groups who demonstrate clinically meaningful cognitive improvement, defined as either ≥5 point improvement on the ACE-III [43], or ≥0.5 SD improvement in the composite *z* score of memory domain in the *Bacopa* versus placebo group at 12 and 24 weeks. Adherence will be monitored through self-reported medication logbooks and weekly telephonic follow-ups.

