**Methods:**

This study will employ a double-blind, randomized, placebo-controlled trial design, with 76 participants (38 per group) of aMCI diagnosed using the clinical National Institute on Aging–Alzheimer’s Association 2011 criteria in a tertiary care setting in India. Participants will receive either *B. monnieri* (Linn.) (300 mg standardized plant extract) or a matched placebo daily for 12 weeks. Comprehensive cognitive assessments (0, 12, and 24 wk) and untargeted plasma metabolomic profiling (0 and 12 wk) will be conducted to evaluate both cognitive changes and alterations in plasma metabolites. MetaboAnalyst 6.0 (with integrated features like Kyoto Encyclopedia of Genes and Genomes and the Human Metabolome Database) will be used for a comprehensive statistical and functional analysis pertaining to the metabolomics. The primary outcome will be a change in the composite *z* score of memory between the 2 groups at 12 weeks. The secondary outcomes will include alterations in metabolites and pathways, and adverse events at 12 weeks, and cognitive performance at 12 and 24 weeks.

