### Need for the Study

aMCI has a high risk of progression to Alzheimer dementia. Currently, there are few approved treatments for aMCI. Antiamyloid agents are the only approved pharmacological options and need sophisticated tests for accurate diagnosis of amyloid pathology in the brain. These drugs are costly, need monitoring for serious adverse effects (SAEs), and are not yet available in low- and middle-income countries. *B. monnieri*, a herb that has been used as a memory enhancer for centuries in India, is a culturally aligned intervention, cheap, and without SAEs. Most studies in the literature on the effectiveness of *Bacopa* on cognitive functions have focused on healthy individuals. Reports in cognitively impaired older adults are few and provide low-certainty evidence. Furthermore, few studies have explored the underlying biological mechanisms of *Bacopa* using the modern “omics” approaches. This study aims to fill these critical gaps by assessing the efficacy of *B. monnieri* (Linn.) in improving memory and other cognitive functions in individuals with aMCI (early or prodromal AD) through an exploratory double-blind randomized controlled trial design. It will also examine related changes in blood metabolites through untargeted metabolomics. We will use a standard *Bacopa* extract containing 50% bacosides, a matching placebo, and culturally valid cognitive tests. The results may contribute to therapeutic strategies for this entity and promote evidence-based traditional medicine within mainstream health care.

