From a safety perspective, Pravina et al [49], in a phase I study, evaluated the short-term safety and tolerability of *B. monnieri* in healthy adult volunteers (aged 22‐42 y) through a randomized, open-label, dose-escalation design. The standardized extract of *B. monnieri* was given to each participant in a dose of 300 mg per day for 15 days, and then 450 mg per day for another 15 days. Pre- and post-treatment examination of clinical, hematological, biochemical, and electrocardiographic parameters of the treated volunteers did not indicate any untoward effects. There were mild adverse events related to the gastrointestinal system in the trial (300 mg dosage: epigastric burning sensation in one volunteer, nausea in one volunteer; 450 mg dosage: fullness and bloating sense of abdomen in one volunteer) which resolved spontaneously without any need to discontinue treatment. There were no dropouts in the study period. At the dose administered for the given duration of the trial period, *B. monnieri* extract was found to be safe in healthy adults. Stough et al [50] have also reported a higher percentage of participants with nausea (18% vs 4%), dry mouth (23% vs 16%) and fatigue (14% vs 4%) in the *B. monnieri* (300 mg for 12 wk) group in comparison to placebo (double-blind placebo-controlled study in 46 healthy volunteers aged between 18 and 60 y). Other studies have reported rash, constipation, drowsiness, and aftertaste following ingestion of *B. monnieri* formulation [25]. Prabhakar et al [51] in their study comparing *Bacopa* to donepezil reported 3 deaths due to myocardial infarction (2 in the donepezil arm and 1 in the *B. monnieri* arm).

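### The abstract names adverse events as a secondary outcome, but Outcomes and the weekly calls cover only serious events, so the non-serious effects the article cites fall outside the safety outcome as written

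*Protocol article*

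**What the plan says.** **Abstract, Methods.** The safety outcome has no seriousness limit: "The secondary outcomes will include alterations in metabolites and pathways, and adverse events at 12 weeks".

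**Outcomes.** The same secondary outcome is narrower: "alterations in metabolites, pathways, and molecular networks, and frequency of SAEs after 12 weeks of treatment with" *B. monnieri*.

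**Follow-Up.** The weekly telephone calls serve to promote retention and to "monitor medication adherence, and collect information on any SAEs". The same section says that a participant with an SAE is told to stop the study medication and that the allocation is then unblinded. At week 12 it schedules "repeat laboratory investigations, including hematological, hepatic, and renal function tests". For participants who leave, "the reason for withdrawal will be clearly documented".

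**Need for the Study.** The abbreviation is expanded once, in a sentence on antiamyloid drugs, which "need monitoring for serious adverse effects (SAEs". The same paragraph describes *B. monnieri* as free of SAEs.

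**Discussion, Principal Findings.** A placebo-controlled study of 300 mg for 12 weeks is reported as showing "a higher percentage of participants with nausea (18% vs 4%), dry mouth (23% vs 16%) and fatigue (14% vs 4" per cent) on *B. monnieri* compared with placebo. Rash, constipation, drowsiness and aftertaste are listed from other studies.

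**Ethical Considerations.** Research-related adverse events are treated free of charge. Nothing is said there about recording them.

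**The concern.** The abstract and the outcome list name different safety outcomes, and the collection procedure described supports only the narrower one. This is a restriction stated in the text, not a detail left to a fuller document.

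The restriction also falls in an awkward place. The article calls the herb free of SAEs, while its own literature summary reports mild, non-serious effects at the same daily dose and duration as this trial. The safety outcome, read literally, counts what the authors do not expect and leaves out what earlier studies found. A reader of the final report could then take a short SAE table as a full account of tolerability. What is at stake is the completeness and interpretability of a secondary safety outcome in an exploratory trial.

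**Working it through.** **1. The texts side by side**

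| Place | What is covered |
|---|---|
| Abstract, Methods | Adverse events at 12 weeks |
| Outcomes | Frequency of SAEs after 12 weeks |
| Follow-Up, weekly calls | SAEs |
| Follow-Up, week-12 visit | Outcome measures; haematology, liver and renal tests |
| Follow-Up, withdrawals | Reason documented |
| Need for the Study | SAE = serious adverse effect |

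The first row cannot agree with the second and third unless SAE means any adverse event. The article's only expansion says otherwise.

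**2. Trying the loose reading.** Suppose SAE was used for side effects in general. Follow-Up would then attach immediate discontinuation and unblinding to every minor event. The literal reading leaves non-serious events outside the outcome and the described calls; the loose reading applies those two steps to nausea or dry mouth. Either way the passages need reconciling.

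**3. The plan's denominator.** Sample Size Estimation: 30 per group with 20% dropout gives 30 / (1 − 0.20) = 37.5, rounded up to 38, or 76 in total. This reproduces.

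**4. Illustrative size.** Input: rates cited in Principal Findings. Assumption: they carry over to this population. Expected participants affected = n × p, Bacopa vs placebo:

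| Effect | Cited rates | 38 per arm | 30 per arm |
|---|---|---|---|
| Nausea | 18% vs 4% | 6.8 vs 1.5 | 5.4 vs 1.2 |
| Dry mouth | 23% vs 16% | 8.7 vs 6.1 | 6.9 vs 4.8 |
| Fatigue | 14% vs 4% | 5.3 vs 1.5 | 4.2 vs 1.2 |

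For nausea at 38: 0.18 × 38 = 6.84 and 0.04 × 38 = 1.52. None of these would enter an SAE-only outcome unless the event met seriousness criteria.

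**5. Imprecision of the cited rates.** The source study had 46 participants. The article gives no split; assuming 23 per arm, the nausea rates are roughly 4/23 and 1/23. Exact 95% intervals are about 5% to 39% and 0.1% to 22%. Over 38 per arm that is about 1.9 to 14.7 on Bacopa and 0.04 to 8.3 on placebo. The 6.8 vs 1.5 is an order of magnitude, not a forecast.

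**6. What full collection would buy.** Power for two proportions, two-sided 5%, normal approximation: Φ[(|p₁ − p₂| − 1.96 × SE₀) / SE₁], with SE₀ = √(2p̄(1 − p̄)/n) and SE₁ = √((p₁(1 − p₁) + p₂(1 − p₂))/n).

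- Nausea, n = 38: p̄ = 0.11, SE₀ = 0.0718, SE₁ = 0.0700; (0.14 − 0.1407)/0.0700 = −0.01; power about 50%.
- Fatigue, n = 38: p̄ = 0.09, SE₀ = 0.0657, SE₁ = 0.0646; (0.10 − 0.1287)/0.0646 = −0.44; power about 33%.
- Dry mouth, n = 38: p̄ = 0.195, SE₀ = 0.0909, SE₁ = 0.0905; (0.07 − 0.1782)/0.0905 = −1.19; power about 12%.

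The benefit is a described adverse event profile by arm, not a test.

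**The case against.** The strongest reply is that the article condenses a fuller protocol. An adverse event form that records everything may exist unseen, and the week-12 visit assesses the secondary outcomes, which by the abstract include adverse events. Withdrawal reasons, prescription changes and laboratory results are further routes. This stands as a limit on the claim, but it does not remove the disagreement between the abstract and the outcome list.

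Several stronger readings are tempting and are not supported:

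- **That non-serious events were never recorded, or that participants who have finished have no such data.** The text says what the calls collect. It does not say that nothing else is written down.
- **That the unnamed laboratory outcome is an error.** The tests are scheduled. Not listing safety laboratory results as an outcome is common in an article.
- **That zero SAEs among 38 leaves an upper 95% limit of 7.6% (1 − 0.05^(1/38)), so the defect is of that size.** The arithmetic is right, but the limit would be the same after the correction, so it does not measure this problem.
- **That the primary result is affected through dropout or guessing of allocation.** No passage shows this, and recording nausea would neither prevent dropout nor protect the blind.
- **That the nausea count is a prediction.** The rates come from healthy adults aged 18 to 60; this trial enrols patients with aMCI aged 45 to 75.

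**Conclusion.** The point holds as an internal contradiction with a concrete consequence. The abstract promises adverse events; the Outcomes section and the weekly calls are limited to serious ones. Followed as written, the safety outcome would leave out the kind of effect that the article itself reports at 300 mg for 12 weeks, although some such events could still surface through withdrawals and laboratory tests. On the assumption that the cited rates transfer, about 7 Bacopa and 1.5 placebo participants out of 38 each would have nausea outside the outcome, with wide uncertainty. The disagreement in wording is certain. Whether data are actually missing cannot be judged from this document. The importance is moderate, because a secondary outcome of a self-described exploratory trial is concerned, but the wording should be corrected before analysis.

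**What to change.** - Reconcile the abstract, Outcomes and Follow-Up by making the outcome all adverse events, with SAEs reported as a subset.
- State that events are recorded at the existing weekly calls and the week-12 visit.
- Report by arm the number of participants with at least one event and the number of events, descriptively, together with the week-12 laboratory results already scheduled.
- Make clear that the discontinuation and unblinding text concerns SAEs as defined, and keep it separate from the recording of non-serious events. This needs no change to any clinical rule.

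**Cost.** A wording amendment and some extra questions on calls already made. The prospective gain is limited: 60 of 76 participants were recruited by November 2025, leaving 16, plus any of the 60 still on treatment. With data collection ending in June 2026 and a 24-week visit, enrolment has to close by about mid-January 2026 (30 June less 168 days is 13 January). If only SAEs were collected up to the change, the data would mix two methods of ascertainment. The report must therefore state which events were collected, how and from when, and disclose any change during the trial. If all events were recorded from the start, only the wording needs correcting.

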### Ethical Considerations

This study has received ethical approval from the Institute Ethics Committee of the All-India Institute of Medical Sciences (AIIMS), New Delhi, India (reference IEC–660/03.09.2021, RP–35/2021). Written informed consent will be obtained from all participants before their enrollment in the study by the clinical psychologist under the supervision of the principal investigator. Participants will be told about the study’s goals, methods, risks, and benefits, as well as their right to withdraw and the steps taken to keep their data confidential. Data will be entered into REDCap (Research Electronic Data Capture), which is a secure web application for managing databases. Any data sharing will involve anonymization of personally identifiable information. All procedures will adhere to the ethical standards established by the institutional review board and the principles outlined in the Declaration of Helsinki. This is an academic, investigator-initiated, nonpharma-funded clinical trial; hence, there is no provision of compensation in the study protocol. However, any adverse event related to the research will be treated free of cost in the hospital.

### Statistical Methods

#### Sample Size Estimation

There are no previous studies investigating the effects of *B. monnieri* versus placebo in patients with aMCI, looking at changes in composite memory *z* scores as the primary outcome. By considering a clinically relevant effect size as a SD change of 0.5, a 2-sided α at 5%, and 80% power, a sample size of 128 (64 in each group) was calculated. With a 20% dropout rate, the final sample size reached 160 (80 in each group), which did not seem feasible for the selected patient population in the specified duration. Therefore, a sample size of 60 (30 in each group) is determined for this exploratory study based on feasibility. The sample size was further adjusted for a dropout rate of 20% and 76 participants (38 in each group) will be recruited for this study.

#### Planned Analyses

As mentioned previously, data will be entered into REDCap, a secure web-based application for managing databases. A data monitoring committee is not needed for this trial, as it is a short-duration study and the known risks of the intervention drug are minimal. No interim analysis is planned. Data will be analyzed using Stata version 17.0 (StataCorp LLC, College Station, TX, USA) and presented data as number (%), mean (SD), or median (IQR), as appropriate. Pearson chi-square test or Fisher exact test will be used (as appropriate) for qualitative variables. For quantitative variables, normality will be assessed using the Shapiro-Wilk test. The Student *t* test for independent samples will be used to compare differences in means for normally distributed quantitative variables. The Mann-Whitney *U* test will be used for quantitative variables with a distribution other than normal. All tests will be 2-tailed, and a *P* value <.05 will be considered statistically significant. Raw scores of each cognitive test will be converted to a *z* score (*z* score=[individual participant raw score – group mean]/group SD) for each participant. The group mean and SD will be derived by pooling the baseline scores of all participants. For all the tests, a higher *z* score will indicate better performance, except for the trail making tests A and B. The signs of these two tests will be inverted for a uniform interpretation. Both intention-to-treat and per protocol analysis will be done. Generalized linear mixed models with a between-subject factor of group (treatment vs placebo) and within-subject factor of time (baseline, mid-point, end point) will be conducted to assess differences in continuous primary and secondary outcome measures. Planned simple contrasts will be conducted to assess all time points (baseline vs. 12 wk, 12 wk vs. 24 wk, and baseline vs 24 wk). To handle any missing data, analysis of last observation carried forward will be undertaken within the intention-to-treat analysis model. Comprehensive statistical and functional analysis pertaining to the metabolomics will be performed using MetaboAnalyst version 6.0. The investigation based on observed peak values will encompass principal component analysis, partial least squares discriminant analysis, ANOVA, and molecular pathway identification. Heat maps will be developed with samples arranged in columns and features in rows, presented in a gradient from cold to hot. Pathway analysis will be conducted utilizing the integrated features of MetaboAnalyst 6.0, which includes the Kyoto Encyclopedia of Genes and Genomes and the Human Metabolome Database.

### 
Reporting Guidelines

The SPIRIT 2025 reporting guidelines have been used while reporting this study protocol. The checklist is provided in Checklist 1. Changes made to protocol after submission to CTRI are summarized in Table S2 in Multimedia Appendix 1.

### 
Dissemination of Results

The results will be presented at scientific meetings and will be published in scientific journals. The results will also be conveyed to the public in simple language during patient awareness programs after study completion.

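### The blanket P<.05 rule makes no exception for the untargeted metabolomics, and the contrast for the metabolite test is not fixed

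*Protocol article*

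**What the plan says.** All of this is in the protocol article.

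- **Significance rule (Planned Analyses):** "All tests will be 2-tailed, and a *P* value <.05 will be considered statistically significant". No adjusted P value, false-discovery rate or other multiplicity rule appears anywhere in the article.
- **Metabolomics analysis (same paragraph):** "Comprehensive statistical and functional analysis pertaining to the metabolomics will be performed using MetaboAnalyst version 6.0", followed by "The investigation based on observed peak values will encompass principal component analysis, partial least squares discriminant analysis, ANOVA, and molecular pathway identification". The factors and form of the ANOVA are not stated.
- **Status (Outcomes):** "The secondary outcomes will include alterations in metabolites, pathways, and molecular networks, and frequency of SAEs after 12 weeks of treatment".
- **Mixed model (Planned Analyses):** "Generalized linear mixed models with a between-subject factor of group (treatment vs placebo) and within-subject factor of time (baseline, mid-point, end point"), intended for continuous primary and secondary outcomes, with contrasts that reach week 24.
- **Sampling (Abstract and Follow-Up):** metabolomic blood is taken at weeks 0 and 12. None is drawn at week 24.
- **Breadth of the assay (LC-MS/MS Methodology, Data Processing):** untargeted acquisition on two columns, each in both ionisation modes. Peaks are kept if their coefficient of variation in pooled quality-control samples is below 30%.

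**The concern.** An untargeted assay produces many tests. A 5% threshold applied feature by feature flags a fixed fraction of the unaffected features however many there are, and the flagged features then feed the pathway step, where chance findings can acquire a biological label. The 30% filter screens measurement quality and does nothing for this error. The results carry weight in the article: metabolites are a named aim, a secondary objective and the stated source of mechanistic insight.

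The second issue is what is being tested. Both arms are sampled twice, so the randomised question is whether the change from week 0 to week 12 differs between arms. The article names ANOVA on peak values but does not say whether that means a group-by-time term, a week-12 comparison of arms, or something else. The one model that states a within-subject factor has three time points, and the blood has two.

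**Working it through.** **Inputs.** From the article: threshold 0.05, two-sided; 30 evaluable participants per arm (Sample Size Estimation). Assumed, because not given: the number of retained features m, the share π of features that truly change, the size of those changes in SD units, and the within-person correlation r.

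**The article's own figures.** It gives no feature count or error rate for the metabolomics, so there is nothing to reproduce there. Its sample-size figures do reproduce: a two-sample t test for 0.5 SD at 80% power needs 63.8, so 64 per arm; 128/0.8 = 160; 30/0.8 = 37.5, so 38 per arm and 76 in all.

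**Step 1: false hits when nothing changes.** Expected number = 0.05 × m.

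| m (assumed) | Expected false hits |
|---|---|
| 100 | 5 |
| 300 | 15 |
| 500 | 25 |
| 1,000 | 50 |
| 2,000 | 100 |

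**Step 2: share of hits that are chance.** Share = (1−π)·0.05 / [(1−π)·0.05 + π·power]. At 30 per arm, two-sample power is 0.478 for 0.5 SD and 0.861 for 0.8 SD.

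| π | 0.5 SD | 0.8 SD |
|---|---|---|
| 5% | 66% | 52% |
| 10% | 48% | 34% |
| 20% | 30% | 19% |

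The share passes one half only when π is below 0.05/(0.05 + power), that is 9.5% for 0.5 SD or 5.5% for 0.8 SD.

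**Step 3: effect of false-discovery control.** Simulation with m = 1,000 independent features, 30 per arm, 200 runs, Benjamini-Hochberg at 5%.

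| Truth | Raw P<.05: hits (false share) | Benjamini-Hochberg: hits (false share) |
|---|---|---|
| no change | 50.1 (all) | 0.08 (all) |
| 5% shifted by 0.8 SD | 90.4 (52%) | 19.4 (4.2%) |
| 10% shifted by 0.8 SD | 130.8 (34%) | 51.5 (4.8%) |
| 5% shifted by 0.5 SD | 71.5 (66%) | 1.1 (2.2%) |

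**Step 4: what ignoring the pairing would do.** Simulation, 30 per arm, 20,000 runs, no true effect, nominal level 5%.

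| r | Type I error, unpaired week 0 v week 12 | Type I error, one-way ANOVA on four arm-by-visit groups |
|---|---|---|
| 0.3 | 1.8% | 3.5% |
| 0.5 | 0.6% | 3.8% |
| 0.7 | 0.1% | 4.2% |

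Both stay below 5%, so ignoring the pairing makes these tests conservative. The price is power: for a 0.5 SD within-arm change with n = 30, a paired test has 61%, 75% and 93% power at r = 0.3, 0.5 and 0.7, against a nominal 48% for the unpaired calculation. If instead the arms are compared at week 12 with baseline ignored, the variance relative to a baseline-adjusted comparison is 1/(1−r²): 1/0.75 = 1.3 at r = 0.5 and 1/0.51 = 2.0 at r = 0.7.

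**The case against.** The strongest defence is that this is a condensed article. A false-discovery threshold, the form of the ANOVA, transformations and validation of the discriminant analysis are ordinary analysis-plan content, and their absence alone is no fault. The P<.05 sentence also closes a list of Stata tests and comes before the separate MetaboAnalyst text, so it may never have been meant for the metabolomics. This stands in part: the omissions are not the point. But the sentence covers all tests without a carve-out, and a later false-discovery rule would have to override it. Exploratory status lowers the stakes but does not remove the problem, because the article calls such results statistically significant and not hypothesis-generating.

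Three stronger readings are tempting, and the article does not support them.

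- **Each person's two samples will be treated as independent.** The article says only ANOVA, without its form, and it plans a within-subject mixed model for continuous secondary outcomes, which can be read to include metabolites. Pairing is unspecified, not excluded, and Step 4 shows that omitting it would not create false hits.
- **Most reported metabolites will be chance.** Step 2 shows that this turns on the share of features that truly change, which is not given.
- **A Bacopa-only before-after test is planned.** The Outcomes phrase about what follows treatment is loose, but it also governs the frequency of serious adverse events, which nobody would read as single-arm. The Discussion ties the mechanistic aim to the randomised design.

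**Conclusion.** The point holds in two parts. First, a stated rule, applied as written, flags about 5 in every 100 unaffected features: 15 to 100 false hits for an assumed 300 to 2,000 features with no true effect. This assumes that the all-tests wording reaches the metabolomics, that the test used is correctly sized, and that significance decides which features go forward to pathway analysis. Second, the metabolite contrast is not fixed: the ANOVA has no stated factors, and the mixed model as written does not fit two sampling times. The consequence there is an open choice of question and a possible loss of power, not extra false positives.

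Severity is moderate. The outcome is secondary, the trial describes itself as exploratory and underpowered, and the primary memory outcome is untouched.

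**What to change.** Change two passages of wording before analysis starts, which the article places after data collection ends in June 2026.

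1. **Error control.** Exempt the metabolomics from the blanket rule. Control the Benjamini-Hochberg false-discovery rate, for example at 5%, over all retained features and over the pathways tested. Label any list based on unadjusted P<.05 as exploratory.
2. **Contrast.** Define the metabolite test as Bacopa versus placebo at week 12, adjusted for the feature's own baseline level and the age stratum. Alternatively, use the group-by-time term over weeks 0 and 12 with participant as the repeated unit.

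No new data are needed. The cost is fewer nominal hits, some of them real. In the simulated case with 5% of 1,000 features shifted by 0.8 SD, the raw list averages 90.4 − 47.6 = 42.8 true hits, while the controlled list has 19.4 hits in all. For 0.5 SD shifts, the controlled list is nearly empty at 30 per arm. That is a reason to use the baseline samples for precision and to keep a clearly labelled exploratory list.
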